## Abstract

**Background:**

Hip fracture patients often have an impaired nutritional status at the time of fracture, which can result in a higher complication rate, prolonged rehabilitation time and increased mortality. A study was designed to evaluate the effect of nutritional intervention on nutritional status, functional status, total length of stay, postoperative complications and cost-effectiveness.

**Methods:**

Open-labelled, multi-centre, randomized controlled trial in hip fracture patients aged 55 years and above. The intervention group receives dietetic counselling (by regular home visits and telephone calls) and oral nutritional supplementation for three months after surgery. The control group receives usual dietetic care as provided by the hospital. Outcome assessment is performed at three and six months after hip fracture.

**Discussion:**

Patient recruitment has started in July 2007 and has ended in December 2009. First results are expected in 2011.

**Trial registration:**

ClinicalTrials.gov NCT00523575

## Background

In the elderly, the incidence of hip fractures is high and it will increase in the nearby future due to the changes in the age demographics, the increased life expectancy and the continuous improvement of health care [1,2]. Hip fractures are one of the most common reasons for hospital admission and transfers to nursing home [3]. Only 37% of the hip fracture patients will return to their pre-fracture functional status, leading to high health care costs and a major burden on health care utilization. These costs are not only determined by acute hospital costs, but even more by the long term costs such as recovery in rehabilitation clinics, the need for home care and the increased burden on informal care givers [4,5].

At the time of hospitalization for a hip fracture, the prevalence of malnutrition ranges from 2% [6] to 63% [7]. Poor nutritional status in hip fracture patients is associated with impaired muscle function, disability [8], loss of independency, lower mental function, decreased quality of life [8], delayed wound healing, higher complication rate [9,10], prolonged rehabilitation time [8,9,11] and increased mortality both during and after hospital admission [9,12-16]. During hospital admission, the nutritional status can deteriorate further due to increased energy expenditure caused by metabolic stress, combined with a low intake due to the lack of appetite, nausea and psychological factors.

In the past decades, several studies have been conducted to determine the effectiveness of various types of nutritional intervention in elderly hip fracture patients on the length of stay, mortality, complications, nutritional and functional status. Results of these studies are inconsistent and the evidence for nutritional supplementation remains limited [17]. Oral nutritional supplementation is the simplest type of nutritional intervention for hip fracture patients to improve the energy and protein intake and nutritional status, although compliance is often poor [18]. Personal attention from a dietetic assistant can improve compliance with and tolerance of nutritional supplements [19] and help to establish a prolonged effect of the nutritional intervention.

The aim of the present study is to investigate the effect of intensive dietary intervention, comprising a combination of dietetic counselling and oral nutritional supplementation during hospitalization and after discharge, on the nutritional status, total length of stay and health care costs after hip fracture. We hypothesize that the combination of dietetic counselling and oral nutritional supplementation in hip fracture patients will improve patients' energy and protein intake, improve their nutritional status, reduce the number of complications and total length of stay in hospital and rehabilitation clinics, and lower health care costs.

## Methods

### Study design, general outline and randomization

Figure 1 shows the design of the study, which is an open-label, randomized controlled, multi-centre trial. Patient allocation to intervention or control group is performed after stratification for hospital, gender, and age (55-74 years vs. 75 years and above). Patients allocated to the intervention group receive dietetic counselling and oral nutritional supplementation for 3 months following surgery. The control group receives usual nutritional care. Patients are enrolled within 5 days after surgical treatment of hip fracture, and baseline measurements are performed immediately after enrolment. Outcome measurements are performed at the patient's home at three and six months following hip fracture. The study has been approved by the Medical Ethical Committee of Maastricht University Medical Centre and Maastricht University and is conducted according to the Declaration of Helsinki.

**Figure 1 F1:**
[figure not shown]
**Study design**.

### Study population and recruitment of the study population

For patient recruitment, a daily inventory is made of hip fracture patients admitted to the surgical and orthopaedic wards of three hospitals in South-Limburg in The Netherlands: Maastricht University Medical Centre, Maastricht (MUMC); Atrium Medical Centre, Heerlen (AMC); and Orbis Medical Centre, Sittard (OMC). Based on this inventory, eligible candidates are invited to participate and written informed consent is obtained within 5 days after surgery. Inclusion criteria are aged 55 years and above and hospital admission for surgical treatment of hip fracture. Patients are excluded if they have a pathological or periprosthetic fracture; disease of the bone metabolism (e.g. M Paget, M Kahler, hyperparathyroidism); life expectancy of less than 1 year due to underlying disease (e.g. cancer); use oral nutritional supplements before hospital admission; are unable to speak Dutch; live outside the region of South-Limburg, or are bedridden before the hip fracture. Patients who suffer from dementia or who are cognitively impaired according to the Abbreviated Mental Test (AMT) (a score of less than 7) are also excluded [20,21].

### Nutritional intervention

The nutritional intervention is a combination of dietetic counselling and oral nutritional supplements for three months. The intervention starts during hospital admission and continues after discharge during the stay at the rehabilitation clinic or at the patient's home. During hospitalization, the study dietician visits the patient twice. At the first visit, two to five days after surgery and immediately after baseline measurements, the dietician interviews the patient regarding medical and social status, and pre-fracture mobility. The dietician also performs a 24-hour recall and takes a general dietary history of the patients' diet before hospitalization. Next, the patient receives the nutritional supplement, a milk-based supplement providing 21 kJ (500 kcal) and 40 g of protein. The dietician advices the patient on the consumption of the supplement and arranges extra care or services to optimize the food intake if necessary. Before hospital discharge, the dietician visits the patient for the second time. During this visit, a 24-hour recall is performed and the consumption of the nutritional supplement is evaluated. Furthermore, arrangements are made to continue the dietetic advice and the consumption of the nutritional supplement at home or during the stay at the rehabilitation clinic. At home or during the stay in a rehabilitation clinic, the dietician visits the patient three times (one week, two weeks and six weeks after discharge) and makes five telephone calls with the patient (three, four, five, eight and ten weeks after discharge). During these visits, food intake and supplement use is assessed by a 24-hour dietary recall, and tailor-made dietetic advice is given to optimize the amount and composition of the diet. As soon as the patient meets nutritional requirements with a normal diet, the use of the nutritional supplement is stopped. Compliance with the nutritional supplement is evaluated by the 24-hour dietary recalls, patients' registration of the consumption in a diary and by collecting the capsules of the cans of the nutritional supplement during the home visits.

### Usual care

Patients allocated to the control group receive usual care as provided in the hospital, rehabilitation clinic or at home, i.e. dietetic care or nutritional supplements are only provided on demand of the medical doctor in charge.

### Outcome assessment

The primary outcome measure is total length of stay in hospital and rehabilitation clinics including hospital readmissions. Secondary outcome measures, assessed at three and six months after hip fracture, are nutritional status, functional status, quality of life, complication rate and one-year mortality.

Assessment of nutritional status includes total food and supplement intake, measurement of body composition, muscle strength and biochemical parameters in blood. Anthropometric measurements are body weight, height, thickness of biceps, triceps, sub scapula and supra-iliac skin fold, and circumference of mid-arm, waist and hip. Body composition is measured by bio-electrical impedance spectroscopy. Biochemical parameters include albumin, pre-albumin, CRP, haemoglobin and hematocrit in blood.

Functional status is measured by the Groningen Activity Restriction Scale (GARS) [22], which assesses disability with regard to (instrumental) activities of daily living, and by the Harris Hip Score to evaluate changes in hip function.

Quality of life is measured using the EuroQoL [23,24] and the Medical Outcomes Study 36-item Short-Form Health Survey [25,26]. Mental state and depression is assessed by the Mini-Mental State Examination (MMSE) and the Hospital Anxiety and Depression Scale (HADS) [27,28]. To measure fatigue, the Checklist Individual Strength (CIS) [29] is used.

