### Statistical analysis

The intervention effects of primary and secondary outcome measures will be analyzed according to the intention-to-treat principle. In addition, a secondary per protocol analysis will be performed in patients with adequate compliance. After initial univariate analyses of differences in the primary outcome between the intervention and control group, multivariate analyses will be used to adjust for potential confounders such as age, gender, baseline values of nutritional status, physical disability, co-morbidity, and mental state including depression.

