## Discussion

Patient recruitment has started in July 2007 and has ended in December 2009. Follow-up of the patients is to be completed in June 2010, except for data of one-year mortality. First results are expected in 2011. We expect that this study will answer the question whether nutritional intervention in hip fracture patients improves their nutritional and functional status, resulting in a shorter length of stay in hospital and rehabilitation clinics, fewer postoperative complications, lower mortality, and cost-effectiveness.

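### As defined, the primary outcome scores an early death as a short stay; fix the counting window and add a supporting analysis that does not reward death

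*Protocol article*

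**What the plan says.** Under Outcome assessment: "The primary outcome measure is total length of stay in hospital and rehabilitation clinics including hospital readmissions". The closing paragraph of the Background fixes the favourable direction. The intervention is hypothesised to "reduce the number of complications and total length of stay in hospital and rehabilitation clinics, and lower health care costs".

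Under Statistical analysis: "The intervention effects of primary and secondary outcome measures will be analyzed according to the intention-to-treat principle". Univariate and then multivariate analyses follow, but no test or model is named for the primary outcome.

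Death enters the article in four other places:
- The Background associates poor nutritional status with "increased mortality both during and after hospital admission".
- One-year mortality is a separate item in the secondary list: "nutritional status, functional status, quality of life, complication rate and one-year mortality".
- The Discussion puts "fewer postoperative complications, lower mortality, and cost-effectiveness" among the matters the study should settle.
- Patients with "life expectancy of less than 1 year due to underlying disease (e.g. cancer") are excluded.

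No sentence says how a patient who dies during the stay, or before a possible readmission, is scored on the primary outcome. No period is given over which readmission days are counted.

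**The concern.** Inpatient days stop accruing at death. Under a plain total, a patient who dies on day 6 scores 6 and a survivor who completes rehabilitation on day 35 scores 35, so the death is the better score. Intention to treat keeps both patients in the comparison.

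If deaths are balanced and stay is unaffected, this does no harm. If they are not balanced, the primary result is distorted:
- Fewer deaths in the intervention arm add inpatient days there and dilute a real reduction.
- More deaths in the intervention arm remove days there and can look like a shorter stay.

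The article itself links nutrition to mortality and asks whether the intervention lowers it, so imbalance cannot be dismissed. Reporting mortality separately makes an imbalance visible but does not correct the primary comparison. Without a common window, the readmission days that enter the total are also undefined.

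**Working it through.** **1. The plan's own figure.** Inputs from the sample-size section: difference 31.3%, SD 59.0%, power 90%, two-sided alpha 0.05.
n per arm = 2 × (1.960 + 1.2816)² × (59.0/31.3)² = 74.7, rounded up to 75. Power at 75 is 90.1%. The stated 75 reproduces, and it contains no allowance for deaths.

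**2. Assumptions the article does not supply.** Mean control stay 40 days; lognormal stay with CV 0.59 (reading the SD as a percentage of the control mean); exponential time to death with mean 14 days (60 days as the alternative); death proportions as shown. A patient who dies contributes the smaller of the stay and the time to death.

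**3. Expected means.** By numerical averaging, a death contributes 12.3 days in an arm with mean stay 40, and 11.0 days in an arm with mean stay 40 × (1 − 0.313) = 27.5.

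True 31.3% reduction, 5% deaths on intervention: intervention mean = 0.95 × 27.5 + 0.05 × 11.0 = 26.7.
- Control deaths 10%: 0.90 × 40 + 0.10 × 12.3 = 37.2; observed reduction 1 − 26.7/37.2 = 28%.
- Control deaths 15%: 0.85 × 40 + 0.15 × 12.3 = 35.8; observed reduction 1 − 26.7/35.8, about 26%.

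No effect on stay, 5% deaths on control: control mean = 0.95 × 40 + 0.05 × 12.3 = 38.6.
- Intervention deaths 10%: mean 37.2; spurious reduction 1 − 37.2/38.6, about 4%.
- Intervention deaths 15%: mean 35.8; spurious reduction 1 − 35.8/38.6, about 7%.

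**4. Simulated consequences** (75 per arm, 4,000 to 6,000 replicates, Monte Carlo error up to about 0.6 of a percentage point). Power is for the t-test on crude days; false favourable results are for the t-test and rank test.

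| True effect | Deaths, control vs intervention | Mean death day | Observed reduction | Significant in favour of intervention |
|---|---|---|---|---|
| 31.3% | 5% vs 5% | 14 | 31% | 95% |
| 31.3% | 10% vs 5% | 14 | 28% | 89% |
| 31.3% | 15% vs 5% | 14 | 26% | 78–79% |
| 31.3% | 15% vs 5% | 60 | 28–29% | 92% |
| none | 5% vs 10% | 14 | 4% | about 6% (nominal 2.5%) |
| none | 5% vs 15% | 14 | 7% | 10–13% |
| none | 5% vs 15% | 60 | 3% | about 5% |

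Power with no deaths is 97% here, above the plan's 90%, because the SD of the intervention arm shrinks with its mean in a lognormal model. The fair baseline for differential mortality is the 95% with equal 5% deaths.

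**5. A second death model.** Let each death contribute a fraction f of the stay that patient would have had, and keep the plan's common SD of 59.
- True 31.3% reduction, deaths 15% vs 5%: observed reduction 27.6% (f = 0.5) to 25.1% (f = 0.2), power 75% to 63%, against 88.6% to 87.7% with equal 5% deaths.
- No effect, deaths 5% vs 15%: spurious reduction 5.1% to 8.3%.
- f = 1: no bias. f = 1.3 (those who die stay longer): the sign reverses, by about 3%.

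**6. Effect of requiring agreement in direction** (t-test on crude days; mean death day 14). With no effect and deaths 5% vs 15%, false favourable claims fall from 11% to about 5% if the supporting analysis ranks death worst, and to about 1% if it compares days alive and out of hospital and rehabilitation over 180 days. With the true 31.3% effect and equal 5% deaths, power is unchanged under the worst-rank condition and falls by about 2 points under the other.

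**The case against.** The strongest objection is that this is a condensed article. It names no test, so time to discharge with death as a competing event, or a rank method, is not ruled out, and an unseen full protocol or analysis plan may contain a rule for deaths. That stands as a limit. A reader might infer that the plan commits to a simple difference in mean days; it does not say so. What remains is the definition that the article does fix: a total of days, with fewer counted as better and deaths kept in.

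A reader might also infer that the sponsor predicts lower mortality. The Discussion says only that the study should answer whether the intervention improves outcomes, with lower mortality among them, and the hypothesis in the Background omits mortality. The link between nutrition and death is an association. Unequal deaths are therefore possible, not stated as expected.

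The exclusions (short life expectancy, cognitive impairment, bedridden before fracture) and enrolment up to 5 days after surgery may keep early deaths modest. That stands, and the later-death rows show how much smaller the problem then becomes.

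The six-month horizon can largely be inferred: outcome visits are at three and six months, costs cover six months, and follow-up ends in June 2010, six months after recruitment closed. The gap is that this is not stated for the primary outcome.

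Finally, ranking death worst changes the question. With no effect on stay and deaths of 15% control against 5% intervention, such a test favours the intervention significantly in about 17–20% of trials, from mortality alone. This is a sound reason not to require it as the primary analysis.

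**Conclusion.** The point holds as an inexpensive improvement. The primary outcome as defined gives an early death a favourable score, and nothing in the article offsets this.

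Under the assumed values with early deaths, a 5- to 10-point mortality advantage for the intervention dilutes the planned 31.3% reduction to about 28% to 26%, with power of about 89% to 78%. The reverse imbalance, with no effect on stay, gives a spurious 4–7% reduction and raises false favourable results from 2.5% to about 6–13%. With mean death at day 60, the figures for 5% vs 15% are about 3% and 5%. The bias disappears if deaths do not shorten the stay, or if deaths are equal and stay is unaffected.

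It would be too strong to say that lower mortality hides a true benefit: the planned effect is diluted, not removed. The loss is more serious for smaller effects. With a true 15% reduction, deaths of 10% vs 5% cut power from about 35% to about 22%. Nor do the documents show that deaths will differ between arms. Every death rate and timing used here is an assumption.

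**What to change.** - State that inpatient days are counted for every patient over one fixed window, from randomisation to six months, and keep length of stay as the primary measure.
- Pre-specify one key supporting analysis that does not reward death: death within the window as worst rank, or days alive and out of hospital and rehabilitation. As a check on direction, the second guarded better against a false claim in the calculation above.
- Report deaths by arm beside the primary result.
- Claim benefit from a shorter stay only if the supporting analysis agrees in direction.

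Recruitment has ended and the trial is open-label, so this should be settled before outcomes are compared by arm.

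The cost is one additional analysis, a more cautious conclusion if the two disagree, and the need to obtain dates of death. The one-year mortality outcome implies that these are available, but the Confounders section lists only admission and discharge dates. The sample size of 75 per arm keeps its basis.

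Making worst rank the primary analysis is an option, not a necessary correction. It costs only about one point of power with equal 5% deaths, but it mixes mortality into the length-of-stay question and detaches the primary analysis from the 31.3% on which the sample size rests.

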### Confounders

Pre-fracture information on co-morbidity, medication use and fracture history is obtained by interviewing the patient. Information on type of hip fracture, surgical treatment, admission and discharge dates, and post-operative complications are obtained from medical charts.

### Economic evaluation

The costs analysis will compare the costs of the nutritional intervention and the usual care over a 6-month period [30]. Medical and non-medical costs are obtained from a 3-month retrospective standardized costing questionnaire. Health care costs will be estimated according to the Dutch guideline for cots-analysis in health care research [31]. Incremental costs between the strategies will be related to a difference in outcome during 6 months follow up and being expressed in a incremental cost-effectiveness ratio. Statistical uncertainty will be assessed using bootstrap simulations [32].

### Process evaluation

A process evaluation is carried out to evaluate whether the nutritional intervention follows the protocol, with regard to the dietetic counselling and the consumption of the nutritional supplement. The feasibility of the nutritional intervention program is evaluated through summative evaluation with the identified stakeholders being patients and health care providers (medical doctors, dieticians, nurses). Experiences and opinions on feasibility, barriers and stimulating or facilitating factors for implementing the nutritional intervention in the transmural care are identified from the stakeholders' perspective. Data are collected by structured interviews with patients and in-depth interviews in a representation of patients and health care providers. A subsample of health care providers is asked to participate in a focus group meeting. The results of the process evaluation will be used as a basis for successful implementation of the nutritional intervention program in the transmural care for hip fracture patients.

### Sample size/power calculation

Nutritional intervention in hip fracture patients can result in an estimated reduction in total length of hospital and rehabilitation stay by 31.3% (SD: 59.0%). A sample of 75 patients per treatment arm is sufficient to detect this effect with a power of 90% and a two tailed alpha of 0.05. To detect a between-group difference in weight of 2.13 kg (SD: 3.72 kg), a number of 61 patients per treatment arm is sufficient using the same power and alpha.

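### The weight sample size of 61 per arm does not follow from its printed inputs, which give 65 per arm; 61 gives about 88% power, not 90%

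*Protocol article*

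**What the plan says.** Under Sample size/power calculation, the protocol article gives two calculations. The first is for the primary outcome, total length of stay: a reduction of 31.3% with SD 59.0%, for which it says "A sample of 75 patients per treatment arm is sufficient to detect this effect". Power for this calculation is set at 90% and alpha at 0.05, two-sided. The second is for weight: "To detect a between-group difference in weight of 2.13 kg (SD: 3.72 kg), a number of 61 patients per treatment arm is sufficient", and the sentence ends by carrying over the settings of the first, since the number "is sufficient using the same power and alpha".

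Under Outcome assessment, length of stay is the primary outcome. Body weight is one of the anthropometric measurements within nutritional status, which is a secondary outcome. The sample size section gives no dropout rate, baseline correlation or other adjustment for either calculation.

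**The concern.** The weight sentence is a complete calculation: it prints the difference and the SD, takes power and alpha from the sentence before it, and prints the result. A reader can therefore check it, and the result is too small for the inputs. The length-of-stay figure, in the same paragraph and at the same power and alpha, checks exactly. Either the number of patients or one of the printed inputs is wrong, or an assumption that the article does not mention was used.

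What is at stake is the accuracy of one power statement. A reader would take it that 61 evaluable patients per arm give 90% power for a 2.13 kg difference, and on the printed figures they do not.

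**Working it through.** **Inputs**, all from Sample size/power calculation:

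- weight: difference 2.13 kg, SD 3.72 kg, taken as the common SD within each arm
- length of stay: difference 31.3%, SD 59.0%
- power 90% and two-sided alpha 0.05 for both
- equal arms, since both numbers are given per treatment arm

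**Formula** (two-sample comparison of means, normal approximation): n per arm = 2 × (1.960 + 1.2816)² / (difference/SD)². The bracket sums to 3.2415, so the numerator is 2 × 10.507 = 21.015.

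**Step 1: the length-of-stay figure is reproduced.** 31.3/59.0 = 0.5305, and its square is 0.2814. Then 21.015/0.2814 = 74.7, so 75 per arm, as stated. This supports reading the printed SDs as within-arm SDs and the method as an unadjusted two-sample calculation.

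**Step 2: the weight figure is not reproduced.** 2.13/3.72 = 0.5726, and its square is 0.3279. Then 21.015/0.3279 = 64.1, so 65 per arm against 61 stated. With the exact t-test, 65 per arm gives 89.97% power and 66 gives 90.4%, so 66 are needed.

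**Step 3: power at given sizes.** Power is approximately Φ[(difference/SD) × √(n/2) − 1.960]. For n = 61 this is Φ(0.5726 × 5.523 − 1.960) = Φ(1.202).

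| Patients per arm | Normal approximation | Exact t-test |
|---|---|---|
| 61 | 88.5% | 88.0% |
| 65 | 90.4% | 90.0% |
| 66 | 90.8% | 90.4% |
| 75 | 93.9% | 93.6% |

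**Step 4: could another route give 61?**

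- Rounding of the inputs: the most favourable unrounded values, 2.135 kg and 3.715 kg, give 63.6, so 64.
- One-sided alpha at 90% power gives 53. A one-sample or paired formula gives 33.
- Two-sided alpha gives 48 at 80% power and 55 at 85% power.
- Allowing for a rank test with efficiency 0.955 gives 64.1/0.955 = 67.1, so 68.
- Some combinations do reach 61: 85% power with 10% added (55 × 1.10 = 60.5), or one-sided alpha with 15% added (53 × 1.15 = 60.95). Each contradicts the stated power or the stated two-tailed alpha, and adds an inflation that the article does not mention.
- Adjustment for a baseline value with correlation ρ multiplies n by (1 − ρ²). Reaching 61 needs 1 − ρ² = 61/64.1 = 0.952, so ρ of about 0.22. No correlation is stated.
- With the other input held fixed, 61 corresponds to an SD of about 3.63 kg or a difference of about 2.18 kg.

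**The case against.** The strongest reply is that nothing in the trial turns on this. Weight is part of a secondary outcome, and the size is set by length of stay. At 75 per arm the power for weight exceeds the stated target. The article's Discussion says that recruitment ended in December 2009. All of this stands. It limits the consequence but does not make the figure right.

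A second reply is that 61 may come from a legitimate calculation whose extra assumption was left out, such as a modest baseline correlation, or from a misprinted input. That also stands as a possibility, so it would be wrong to say that 61 can be right only under a different SD or difference. It does not rescue the sentence as printed, because the sentence offers the difference, SD, power and alpha as the basis for the number.

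A reader might draw three stronger conclusions, and the article supports none of them:

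- *That the trial is underpowered for weight.* It is not at 75 per arm, if all are evaluable.
- *That the gap between 75 and 61 was the allowance for deaths and withdrawals on weight, and is overstated.* The article states no attrition margin and no number enrolled, and does not present the gap as an allowance. A journal article may leave attrition to the full protocol.
- *That 66 is the number to print.* By the t-test, 75 per arm gives 89.75% power for length of stay, and 76 would be needed. Printing 66 next to 75 would put the two sentences on different methods. On the method that reproduces 75, the matching figure is 65.

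**Conclusion.** The point holds as an error in a stated figure. The number for weight is four patients per arm too low, 61 against 65, which is 4/65 or about 6% of the requirement. The shortfall in power at 61 is 1.5 points by the normal approximation and 2.0 by the t-test. The conclusion rests on a two-sample comparison of means, equal arms, a within-arm SD of 3.72 kg and no covariate adjustment. The length-of-stay calculation supports that reading, because it reproduces exactly under it.

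The documents do not show which element is wrong: the number, an input, or an unstated assumption. The weight is minor: it is a reporting correction with no effect on the 75 per arm or on the primary outcome.

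**What to change.** Make the sentence consistent with its inputs in one of these ways:

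- replace 61 with 65 per arm, on the same method as the 75
- keep 61 and give its power as about 88%
- keep 61 at 90% power, and state the corrected difference or SD, or the extra assumption (for example a baseline correlation), that produces it

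If the t-test is preferred, use it for both outcomes, which gives 76 for length of stay and 66 for weight. The sponsor's original calculation, if it is on file, would settle which of these applies. The cost is one corrected figure or one added clause, with no change to enrolment or analysis.
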